### Statistical analysis

All data analysis will be performed using SPSS Statistics v21.0 (IBM). To ensure that they are blinded to group assignment, the outcome assessors and data analysts will not interact with the participants except during data collection (in the case of outcome assessors). Demographic and other baseline characteristics will be summarized using descriptive statistics. If necessary, the results will be adjusted for potential confounders, such as age, gender, and education. Quantitative data will be expressed as frequencies or rates and statistical analysis will be carried out using the *χ*^2^ test. If these data are normally distributed, they will be expressed as (*x* ± *s*). The effects of the interventions (between-group differences) will be calculated with linear mixed models using interaction terms (group allocation versus time), which are equivalent to the between-group differences. The within-group differences will be calculated using repeated measures ANOVA. *P*-values < 0.05 will be considered statistically significant. The data will be reviewed before analysis. The Statistical Package for the Social Sciences (SPSS) software will be used for all analyses. The clinical relevance of the results will be confirmed by calculating the effect size (Cohen d) of the significant differences found between the assessments. The following effects will be considered: small: 0.00–0.49; medium: 0.50–0.79; high ≥0.80 (Cohen, 1988). Comparison between the four subgroups within the intervention group using ANOVA test.

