## Methods

### Trial design

This is a single-blind, two-arm randomized controlled trial with randomization at the participant level. Participants will be randomly allocated to receive a HMI (control) or a SISMT (intervention). Primary and secondary study outcomes will be collected for both groups at baseline (T0) and 12 weeks(T1), 24 weeks post-intervention(T2). As the study involves the older adults with MCIs, a few specific ethical procedures should be followed and ensured. Only those who signed the consent form can be included in this study, and a guardian as the legal representative should be asked to co-sign the consent form. The trial has been registered at ChiCTR.org.cn (ChiCTR2200061991, date:16/07/2022).

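### Cohen d is calculated only for significant differences, which inflates it, and covariate and baseline adjustment of the group-by-time model is left open

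*Protocol article*

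**What the plan says.** All but one of the relevant statements are in the Statistical analysis section of the protocol article.

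- **Treatment effect.** It comes from "linear mixed models using interaction terms (group allocation versus time), which are equivalent to the between-group differences". Under Trial design, "Primary and secondary study outcomes will be collected for both groups at baseline (T0) and 12 weeks(T1), 24 weeks post-intervention(T2"), so the baseline visit is one of the times at which the outcome is measured. No baseline covariate, and no constraint on the baseline means, is stated.
- **Covariates.** "If necessary, the results will be adjusted for potential confounders, such as age, gender, and education". No criterion says when adjustment becomes necessary, and the list is open-ended.
- **Significance.** P-"values < 0.05 will be considered statistically significant".
- **Effect size.** Clinical relevance will be "confirmed by calculating the effect size (Cohen d) of the significant differences found between the assessments". The bands are small 0.00–0.49, medium 0.50–0.79 and high from 0.80.
- **Descriptive rule.** "Quantitative data will be expressed as frequencies or rates and statistical analysis will be carried out using the" chi-square test. The next sentence gives mean and SD for the same data if they are normally distributed.

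**The concern.** The effect-size rule selects on significance. In a small trial only large observed differences pass that filter, so the d values that appear are too large on average. The protocol then uses those same values as its evidence of clinical relevance.

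The covariate rule leaves the choice between an adjusted and an unadjusted result open until the data are seen. In a randomised trial covariates are best fixed in advance because they are prognostic, not added as confounders when someone judges it necessary.

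The model statement leaves the handling of baseline open. The usual fit, with free baseline means, estimates a difference in change. That can be less precise than a model that uses the baseline value as a covariate or constrains the baseline means to be equal.

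**Working it through.** **Inputs.** From Sample size calculation: HbA1c 6.49 ± 1.59 against 6.97 ± 0.73, and 34 evaluable per group. Two-sided 5% is assumed, because sidedness is not stated. The correlation r between baseline and follow-up is not in the document; 0.3 to 0.9 is assumed.

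**The plan's own figures.** Difference 0.48; pooled SD = √((1.59² + 0.73²)/2) = 1.237; d = 0.48/1.237 = 0.39. These inputs give 140 per group for 90% power (two-sided, pooled SD), so the stated 34 does not reproduce. That is a separate matter. It bears on this point only because low power strengthens the filter.

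**1. Significance filter, post-score comparison, 34 per arm.** Smallest significant |d| = t(0.975, 66) × √(2/34) = 1.997 × 0.2425 = 0.48. By simulation:

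| True d | Significant | Mean d when significant |
|---|---|---|
| 0.20 | 13% | 0.59 |
| 0.39 | 35% | 0.66 |
| 0.50 | 53% | 0.69 |
| 0.80 | 90% | 0.86 |

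Without the filter, the mean d at a true 0.39 is 0.39. At 43 per arm the threshold is 0.43 and the filtered mean for a true 0.39 is 0.59.

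**2. The same filter under a change contrast.** With equal variances, and d expressed on the post-score SD, the standard error is √(2(1−r)) × √(2/34). True d 0.39, 34 per arm:

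| Assumed r | Smallest significant d | Mean d when significant | Inflation |
|---|---|---|---|
| 0.3 | 0.57 | 0.74 | 1.9-fold |
| 0.5 | 0.48 | 0.65 | 1.7-fold |
| 0.7 | 0.38 | 0.53 | 1.4-fold |
| 0.9 | 0.22 | 0.40 | 1.03-fold |

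**3. Precision of the treatment contrast.** With equal variances at the two visits, the change contrast has variance proportional to 2(1−r), and the baseline-adjusted contrast 1−r². The ratio is (1+r)/2. A three-visit mixed-model calculation with the baseline means constrained equal gave the same ratios. Power is for an illustrative d = 0.5 at 34 per arm.

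| Assumed r | Variance saved | Power, change → adjusted |
|---|---|---|
| 0.3 | 35% | 41% → 58% |
| 0.5 | 25% | 54% → 66% |
| 0.7 | 15% | 76% → 82% |
| 0.9 | 5% | 99.6% → 99.7% |

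**4. Effect of entry limits.** The equal-variance formula fails when entry restricts the baseline score. Let s₀² be the baseline variance, b the slope of follow-up on baseline and e² the residual variance. The change has variance s₀²(1−b)² + e², the adjusted contrast e². Restricting a standard normal baseline to a 1-SD band makes s₀² about 0.081. At an unrestricted r of 0.5, b = 0.5 and e² = 0.75, so the excess is 0.081 × 0.25 = 0.020 and the saving is 0.020/0.770 = 2.6%. At unrestricted r of 0.3 and 0.7 the savings are about 4% and 1.4%.

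**5. Time-constant covariates.** Adding education as a main effect leaves the standard error of the group-by-time term unchanged (0.2425 with and without it at r = 0.5, complete data), because it cancels in a change contrast.

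**The case against.** The strongest objections concern precision, and most of them stand.

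- A group-by-time mixed model is valid under randomisation. The wording also fits a model with constrained baseline means, which already has the smaller variance. The full protocol or analysis plan may settle this, so a reader might infer that the plan commits to an unadjusted change contrast, but the text does not establish it.
- A reader might infer that the narrow MoCA and MMSE entry limits lower r and so make the loss largest here. Step 4 shows the reverse for a restricted baseline: its variance shrinks too, and little is left to save. Pooled MoCA is different, because Diagnosis criteria admits three separate education-specific bands and pooled scores may be widely spread. The document does not say what r results.
- A reader might also infer that leaving out age, gender or education wastes precision. Step 5 shows that it does not in a change contrast. The defect there is only the open choice.

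On effect sizes, the inflation depends on r and nearly vanishes at 0.9. The phrase about differences between the assessments may refer to within-group changes over time. The plan makes only Cohen d conditional on significance; it does not say that non-significant model estimates go unreported. These points limit the size of the bias, but the selection rule is stated outright and applies under either reading.

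**Conclusion.** The point holds for what the section states. Calculating Cohen d only for significant differences biases it upward: for a true d of 0.39 at 34 per arm, the mean reported between-group value is 0.40 to 0.74 over assumed r of 0.9 down to 0.3 under a change contrast, or 0.66 for a post-score comparison. This assumes two-sided 5%, equal variances, and d on the post-score SD.

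The covariate condition permits either an adjusted or an unadjusted result. No size can be put on that.

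Use of the baseline value is a worthwhile improvement of unknown size: 5% to 35% of variance with equal variances, and possibly only a few per cent for MMSE, or for MoCA within education bands. The documents do not support a claim that precision is lost by a known amount, or that entry restriction enlarges the loss.

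The chi-square sentence is a wording error: that rule fits categorical data.

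**What to change.** - Prespecify one primary mixed model for T1 and T2 with the baseline value of the outcome as a covariate (or with T0 kept as an outcome and its group means constrained equal), a fixed covariate list, group, visit and group × visit.
- Delete *If necessary* from the covariate sentence.
- Report the between-group estimate, its 95% CI and Cohen d for every planned outcome and visit, whatever the p-value.
- In the chi-square sentence, change *Quantitative data* to *Categorical data*.

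The cost is a few degrees of freedom and more estimates to report. The baseline assessment already precedes randomisation, so no new data are needed.

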**Discussion:**

This study developed a stratified support pattern-based internet-assisted to provide self-management intervention for patients with DM-MCI. The impact of different models and forms of self-management intervention on cognitive function, blood glucose management, and psychological status health literacy and self-management behavior of patients will be assessed. The results of this study will inform related intervention research on the stratified support pattern-based internet-assisted self-management therapy, and help to slow the decline of cognitive function in patients with DM-MCI.

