## Background

Diabetes mellitus (DM) is one of the chronic diseases that develop rapidly and threaten global health. According to the data of the International Diabetes Federation (IDF) in 2021, about 537 million adults (20–79 years old) worldwide suffer from diabetes, which will rise to 783 million by 2045. During this period, the world population is estimated to increase by 20%, while the number of patients with diabetes is estimated to increase by 46% [1]. It can be seen that the form of diabetes is not optimistic. DM is characterized by persistent hyperglycemia, which will not only cause chronic damage to blood vessels, brain and other tissues and organs [2, 3], but also affect the nervous system function of patients, thus causing cognitive impairment [4]. Some studies have further proved the correlation between this disease and found that most diabetes patients will have cognitive impairment, and 25–36% of them have mild cognitive impairment (MCI) [5]. Some research teams have called this type of patient as DM-MCI [6–8], and one of research teams conducted a survey on the prevalence of this type of patient. It was found that the overall prevalence of DM-MCI is 45%, indicating that DM-MCI is affecting residents on a large scale [8].

MCI refers to a stage in which a patient's cognitive function has been impaired, but its severity is not sufficient to constitute dementia, and it is a precursor to the development of dementia [9]. According to statistics, the global prevalence of elderly MCI is approximately 3–22%, with approximately 5–10% of these patients developing dementia annually [10, 11]. As one of the risk factors for cognitive impairment, diabetes not only increases the risk of cognitive impairment, but also accelerates the disease progression of MCI. Fortunately, mild cognitive function has a characteristic of bidirectional transformation. It means that MCI is an intervention stage in disease progression [12]. And a study has found that MCI patients' self-management ability related to blood glucose control is poor, which will affect the blood glucose control of patients. This undoubtedly further accelerated the progress of cognitive impairment in patients with DM-MCI [13]. Therefore, improving self-management ability has become an important measure to prevent the deterioration of disease in patients with DM-MCI.

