### Participants

#### Recruitment and screening

By convenient sampling, patients with DM will be screened for MCI and included in the study. This study is approved by relevant hospital departments and most patients were recruited from the endocrine clinic at a provincial Third-Grade Class-A General Hospital. The study researchers will met with DM patients who were visiting the clinic and asked them to complete the Montreal Cognitive Assessment (MoCA) [35], the Mini-Mental State Examination (MMSE) [36], the diabetes self-management scale (DSCS) [37], and the Activity of Daily Living (ADL) survey [38], along with a general information questionnaire. The questionnaires will be completed in separate rooms of the hospital. So far, 240 DM-MCI patients have been screened.

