AVLT	This study adopts the Chinese version of AVLT developed by Guo Qihao and others from Shanghai Huashan Hospital, which has good reliability and validity and has important application value for clinical guidance and scientific research. The operation of this scale mainly involves the researcher reading 12 words: coat, driver, pants, crabapple, carpenter, lily, headscarf, wintersweet, soldier, magnolia, lawyer, and glove. After each reading, the patient is asked to repeat as many words as possible and record them. The number of repeated words in the 3 times is added as the instant memory quantity (i.e. N1 + N2 + N3); After 5 min, ask the patient to recall 12 words and say if they still remember them. The researcher recorded the number as short-term memory (N4); After 20 min, ask the patient about the number of words they remember as long-delayed memory (N5); Finally, a re-recognition test was conducted, with a total of 24 words and 50% of the vocabulary with 12 interfering items. The patient responded with "said" or "not said", and the researcher determined that each correct answer scored one point
SDMT	SDMT is commonly used for testing attention, learning, and conversion abilities. This test is a numerical symbol subtest in the revised Wechsler Adult Intelligence Revised in China (WAIS-RC), which reflects the information processing speed of the subject. During the testing process, participants were provided with a piece of paper with a template containing 9 digits, each with its corresponding symbol. The test requires patients to fill in as many and as quickly as possible the corresponding numbers of the symbols in the spaces below the numbers. The subjects should fill in as many and correct numbers as possible within 90 s. When it's time to calculate the correct number, the higher the score, the better the tester's attention and conversion ability

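### Within-arm change is tested for significance, and the Cohen d rule for clinical relevance is not limited to the between-arm difference

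*Protocol article*

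**What the plan says.** The Statistical analysis section defines the intervention effect as the group-by-time interaction in a linear mixed model. It then adds a second inferential step: "The within-group differences will be calculated using repeated measures ANOVA". One significance threshold, P < 0.05, is given for all tests. A third step follows: "The clinical relevance of the results will be confirmed by calculating the effect size (Cohen d) of the significant differences found between the assessments", with the labels "small: 0.00–0.49; medium: 0.50–0.79; high ≥0.80".

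Four other places bear on how these sentences work:

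- **Diagnosis criteria.** Entry requires a MoCA of 13–14, 19–20 or 24–25, depending on education. Table 3 puts normal at 26 or above, so every band lies below it. The MMSE requirement is 24–30.
- **Primary outcomes and Trial design.** MoCA and MMSE are the primary outcomes, taken at baseline (T0), 12 weeks (T1) and 24 weeks (T2).
- **Background.** "Fortunately, mild cognitive function has a characteristic of bidirectional transformation".
- **Table 3, AVLT.** The test is described with a single printed list: "the researcher reading 12 words: coat, driver, pants, crabapple, carpenter, lily" and six more words.

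**The concern.** Randomisation protects the comparison between arms. It does not protect the comparison of one arm with its own baseline. Anything that moves scores over 12 or 24 weeks in everyone appears in full in the within-arm change: natural course of a condition that can revert or progress, familiarity with a test taken before, and regression to the mean if the score that admitted the patient also serves as T0.

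The plan tests that change and then uses an effect size to confirm clinical relevance. Nothing restricts the effect size to the between-arm contrast. The labels start at zero, so every significant difference receives a size. Followed as written, the rule allows a change in the SISMT arm that is not due to the intervention to be called significant and clinically relevant, even where the two arms do not differ.

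**Working it through.** **1. What the clinical-relevance rule covers.** The phrase is "calculating the effect size (Cohen d) of the significant differences found between the assessments". Trial design and the outcome timeline describe measurement occasions at T0, T1 and T2, and the randomisation section speaks of a baseline assessment. Differences between assessments are therefore, on the natural reading, differences over time. The sentence comes after the one on within-group ANOVA, and no text confines d to the arm contrast. The wording is loose, so this is the most natural reading and not an explicit statement.

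**2. How easily a within-arm test turns significant.** Take n = 34 per arm (the evaluable number in Sample size calculation) or 43 (the number recruited per arm there). Let d be mean change divided by the SD of change, and use a paired two-visit test as a simple stand-in for the three-visit ANOVA. The chance of a significant rise is P(T > t₀.₉₇₅), where T is noncentral t with n − 1 degrees of freedom and noncentrality d√n.

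| Non-treatment change, d | n = 34 | n = 43 |
|---|---|---|
| 0 | 2.5% | 2.5% |
| 0.2 | 20% | 25% |
| 0.3 | 40% | 49% |
| 0.5 | 81% | 89% |

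At n = 34 the critical t is 2.03, so any significant two-visit change has an observed d of at least 2.03/√34 = 0.35.

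**3. Regression to the mean alone, upward case.** Assumptions not in the documents: MoCA SD 3, clinic mean 1, 2 or 3 points above the centre of a two-point entry band, screening score used as T0, no intervention effect. Reliability is set at 0.83, the Cronbach's alpha in Table 3, as a stand-in for retest reliability.

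- Expected rise ≈ (1 − 0.83) × distance = 0.17, 0.34, 0.51 points. Simulation over the band gives 0.16, 0.33, 0.49.
- SD of change ≈ 3 × √(1 − 0.83²) = 1.67; simulated, about 1.68.
- d ≈ 0.16/1.68, 0.33/1.68, 0.49/1.68 = 0.10, 0.20, 0.29.
- Noncentrality d√34 ≈ 0.56, 1.15, 1.70.
- Chance of P < 0.05 (two-sided) ≈ 9%, 20%, 38%, against a nominal 5%.

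**4. A retest gain alone.** Suppose T0 is measured afresh, so that regression to the mean drops out, and assume a gain of 0.5 point from repeated testing. The SD of change is then 3 × √(2 × 0.17) = 1.75, d = 0.5/1.75 = 0.29, and the chance of P < 0.05 is about 37%. The gain is an assumption; the documents give no figure.

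**5. Direction is not fixed.** A second simulation with no effect in either arm used SD 4, population mean 22, 24 or 26, reliability 0.7, 0.8 or 0.9, screening score as T0 and 34 per arm.

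| Entry rule | Mean change (points) | Significant rise | Significant fall |
|---|---|---|---|
| Printed band 24–25 | −0.76 to +0.40 | 0–13% | 0.2–32% |
| Any score ≤ 25 (for comparison) | +0.14 to +1.05 | 6–53% | 0–0.8% |

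In every scenario the between-arm test of change rejected in 4.7–5.2% of trials.

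**The case against.** The strongest reply is that the plan already does the right thing where it matters. The intervention effect is the between-arm interaction, the hypotheses all compare SISMT with HMI, and no sentence says that within-arm change is evidence of efficacy. The control arm's own change would be visible beside it. This stands, and it limits the point to the supplementary tests and the clinical-relevance rule. It does not remove the point, because that rule is stated and its wording reaches within-arm change.

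Three stronger readings are tempting, and the documents do not support them.

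- **A reader might infer that scores in both arms must rise.** The bands have lower as well as upper limits and the clinic mean is not given, so regression can go either way. Movement in both directions is not net improvement. The randomisation section lists eligibility screening and baseline assessment as separate steps, which favours a fresh T0. MMSE 24–30 is a floor, not selection on a low score.
- **A reader might infer that a false within-arm finding is close to certain.** Adding an assumed retest gain of 0.5–1.0 point to the upward regression in step 3 gives 61% to over 99%, but that gain has no source in the documents.
- **A reader might set the abstract's hope to "help to slow the decline of cognitive function in patients with DM-MCI" against the yearly rate of conversion to dementia in the Background and conclude that no decline could be seen.** That sentence is an aspiration, not a hypothesis, and conversion to a diagnosis does not measure decline in MoCA or MMSE score.

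**Conclusion.** The point holds in a limited form. The group-by-time interaction is unaffected by natural course, retest effects or regression to the mean, so the primary comparison is not in question. The within-group significance test and the Cohen d rule are badly fixed: they allow significance and clinical relevance to be attached to a change that randomisation does not protect.

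The size depends on inputs the documents do not give. Under the assumptions in step 3, within-arm P < 0.05 arises by upward regression alone in about 9–38% of trials with no intervention effect, and more often with any retest gain on top. Under the assumptions in step 5 a significant fall is also possible. Either way, within-arm change cannot be read as an intervention effect. The conclusion also rests on reading assessments as time points, which fits the protocol's usage but is not stated outright. The change is worth making because it alters what the trial may claim.

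**What to change.** In the Statistical analysis section:

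1. Report within-arm change descriptively, as mean change with a confidence interval for each arm and visit.
2. Remove the within-group repeated measures ANOVA as a significance test.
3. State that Cohen d and any statement on clinical relevance refer only to the between-arm difference.

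The linear mixed model stays as it is. The cost is a few lines of wording, with no new data, patients or visits. The one loss is that within-arm p-values are no longer reported.

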### Sample size calculation

The required sample size is estimated using PASS v11.0 (NCSS, Kaysville, UT, USA) based on a completely random design for comparing the means of two independent samples. To our knowledge, there is no previous study on a stratified support pattern-based internet-assisted self-management therapy for DM-MCI in mainland China, so we estimate the effect size of one of the outcomes (HbA1c) based on previous research on patients with DM-MCI [42]. This study find that HbA1c scores in intervention and control group are 6.49 ± 1.59 and 6.97 ± 0.73, respectively. A sample size of 34 participants per group was determined to be sufficient to detect an effect with a type 1 error rate of 5% (α = 0.05) and 90% power (β = 0.1). A total of 68 participants will be needed, with 34 participants per group. Considering a 20% loss of follow-up rate, the final sample size is 86, with 43 participants per group.

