### Criteria for discontinuing or modifying

During the intervention period, if the participant is unwilling to continue due to personal reasons, the intervention will be terminated. Participants who are unable to continue but are willing to undergo follow-up will be modified for intervention measures and replaced with a control group.

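### Within-arm changes from repeated measures ANOVA would be completers-only figures, although the mixed model already planned can supply them from all available visits

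*Protocol article*

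**What the plan says.** The Statistical analysis section names two methods for the same repeated outcomes. For the comparison of arms: "The effects of the interventions (between-group differences) will be calculated with linear mixed models using interaction terms", the interaction being group by time. For change inside an arm, the next sentence reads "The within-group differences will be calculated using repeated measures ANOVA". All analysis is to be done in SPSS v21.0.

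The Trial design section and the outcome timeline set three assessments: baseline (T0), 12 weeks (T1) and 24 weeks (T2). The Sample size calculation section expects attrition: "Considering a 20% loss of follow-up rate, the final sample size is 86, with 43 participants per group". The section on objectives and hypotheses states every hypothesis as SISMT against HMI at 12 weeks. The article names no imputation and no analysis set for either method.

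**The concern.** The two methods treat a missed visit differently. The usual repeated measures ANOVA in SPSS needs a value at each of the three visits and removes the whole participant if one is absent. A likelihood-based mixed model keeps each visit that was observed. Someone who attends T0 and T1 and then misses T2 has a fully measured 12-week change, at the time point on which the hypotheses are set. The ANOVA discards that change because of a later visit.

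What is at stake is the reported within-arm change. It would describe those who returned at week 24, a subset of the participants behind the between-group estimate. The difference between the two reported within-arm changes then need not equal the between-group effect printed beside them. The same section also plans Cohen d for significant differences between assessments. That can be read as covering within-arm comparisons, so a completers-only figure could support a remark on clinical relevance.

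**Working it through.** **1. The plan's own figure.** The section starts from 34 per group: 34 / (1 − 0.20) = 42.5, rounded up to 43 per group, 86 in total. This reproduces. (How the 34 was derived is a separate matter and is not used here.)

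**2. Participants with all three visits at that loss.** 86 × 0.80 = 68.8, about 34 per arm (43 × 0.80 = 34.4). Left out: 86 × 0.20 = 17.2, about 17. With the 84 given in the Abstract, 84 × 0.20 = 16.8, again about 17. The 20% is not tied to a visit, so 17 is what the allowance implies if each lost participant misses at least one of T1 and T2.

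**3. What each method uses.**

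| Visits observed | Repeated measures ANOVA | Linear mixed model |
|---|---|---|
| T0, T1, T2 | all | all |
| T0, T1 | nothing | T0 and T1 |
| T0, T2 | nothing | T0 and T2 |
| T0 only | nothing | T0 |

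The ANOVA set lies inside the mixed-model set. The second row is where an observed 12-week change is lost.

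**4. If loss is unrelated to outcome.** There is no bias. If all of it falls after T1, the 12-week change rests on about 34 rather than 43 per arm, so its standard error grows by a factor of √(43/34) = 1.12.

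**5. If loss depends on the week-12 score (assumed).** Take scores with SD 1 at each visit, equal correlation r between visits, no true change, and 20% missing at T2 only, with log-odds of loss falling by b per SD of the T1 score. Because E[T0 | T1] = r·T1, the completers' mean change from T0 to T1 is (1 − r) × E[T1 | kept]. Numerical integration gives E[T1 | kept] = 0.130 for b = 0.7 and 0.227 for b = 1.5. The standard error at 34 completers is √(2(1 − r)/34).

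| r | Bias, b = 0.7 | Bias, b = 1.5 | SE | Bias / SE |
|---|---|---|---|---|
| 0.5 | 0.065 | 0.113 | 0.171 | 0.38 to 0.66 |
| 0.7 | 0.039 | 0.068 | 0.133 | 0.29 to 0.51 |
| 0.8 | 0.026 | 0.045 | 0.108 | 0.24 to 0.42 |

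The range is therefore about 0.03 to 0.11 SD, in the direction of apparent improvement on a scale where higher is better. Under this equal-correlation set-up the T0 to T2 change of completers is not biased, since E[T2 − T0 | T1] = 0. The distortion falls on the 12-week change.

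A separate simulation with a true change of 0.30 SD, r of 0.5 and 0.7, and steeper slopes (1 and 2) gave 0.35 to 0.43 among completers. The estimate from all available visits stayed at 0.30.

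**6. If half the loss comes before week 12.** Suppose 10% of participants leave before T1 at random and a further 10% after it, that is, one in nine of those seen at T1. Then E[T1 | kept] is 0.074 (b = 0.7) or 0.134 (b = 1.5). The bias runs from 0.2 × 0.074 = 0.015 to 0.5 × 0.134 = 0.067 SD.

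**The case against.** Several objections have force.

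- **No hypothesis rests on this analysis.** All stated hypotheses compare the arms and go to the mixed model, which handles this pattern of loss. This stands. A reader might infer that the primary result is at risk; the document does not support that.
- **An unseen plan may add imputation, or run the ANOVA on T0 and T1 alone.** Either would keep some or all of the participants in question. It is therefore too strong to say that they cannot be analysed. The point is conditional on the standard form without imputation, which is the plain reading of the method named.
- **The bias figures are assumed.** Timing, direction, slope and correlation are not in the article. Even the top of the range, 0.11 SD, is far inside the band of 0.00 to 0.49 that the plan itself calls small. The absence of bias in the mixed model also follows from the assumed mechanism, in which loss depends only on observed scores.
- **Selection by arm.** A reader might infer that completers are selected differently in the two arms, because participants can stop SISMT: "if the participant is unwilling to continue due to personal reasons, the intervention will be terminated". The document does not support this. That sentence ends the intervention, not the assessments, and the next one provides for people who cannot continue but accept follow-up. The 20% allowance is the same for both arms.
- **Different patients.** A reader might say that the two methods rest on different people. More exactly, one set is a subset of the other.

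What remains is that the article names a weaker method for within-arm change when a better one is already planned.

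**Conclusion.** The point holds as a minor improvement to supporting results. Under standard SPSS repeated measures ANOVA without imputation, and at the plan's own 20% allowance, up to about 17 of 86 participants leave the within-arm analysis. The within-arm changes become completers-only figures that need not agree with the between-group effect. The between-group tests are unaffected.

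The loss of participants and the possible mismatch need no assumption about why people leave. Bias does: it arises only if loss is related to outcome. The range of about 0.03 to 0.11 SD requires all loss to fall after week 12 and to depend on low week-12 scores.

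**What to change.** Replace the sentence on repeated measures ANOVA with one stating that within-arm changes from T0 to T1 and from T0 to T2 will be estimated, with 95% confidence intervals, as contrasts from the linear mixed model that gives the between-group effect, using all available visits. With group, time and their interaction in one model, the difference between the two within-arm contrasts is the between-group effect, so the figures agree by construction.

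The cost is one sentence and an extra set of contrasts from a model already planned. No further data or participants are needed. The output is slightly less familiar than an ANOVA table.
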